**Figure 1 F1:**
[figure not shown]
Study flowchart showing allocation to groups.

### Measures

#### Socio-demographics

In the initial meeting the following data are registered: date of birth, height, weight, ethnicity, number of children, level of education, marital status, employment status, smoking, drinking, exercise participation, medication, and medical treatment history (including any treatments for HF/NS).

#### Primary outcome

The self-reported problem-rating of HF/NS (Hot Flush Rating Scale, or HFRS [18]) at post treatment will constitute the primary outcome; the score is the mean of 3 items (i.e., ‘*To what extent do you regard your flushes/sweats as a problem?*’, ‘*How distressed do you feel about your hot flushes?*’, and ‘*How much do your hot flushes interfere with your daily routine?*’) are rated on a 10-point Likert scale where a higher score indicates that the patient views his HF/NS as highly bothersome and interfering with life. A difference of 2 points or more is considered clinically relevant [9,10,19].The scale has good internal consistency in studies with women (Cronbach alpha=0.9) and test-retest reliability (r = 0.8). The problem-rating is chosen as the prime outcome measure because it, rather than frequency, is associated with help-seeking and quality of life, and in recent studies problem-rating has been recommended as the most appropriate patient reported outcome measure in clinical trials of HF/NS treatments [20,21]. Problem-rating and severity tend to be correlated and neither are strongly associated with frequency of HF/NS [21].

#### Secondary outcomes

The problem-rating of HF/NS described above will be measured again at the 6-month follow-up session as a secondary outcome.

Self-reported frequency of HF/NS is assessed by a subscale of the HFRS which measures the total number of HF/NS reported in the past week. This subjective HF/NS frequency measure was found to correlate (r = 0.9, p < 0.0001) with daily diary recordings of HF/NS in a previous study [18].

Quality of life (QOL) is assessed using both the 30-item EORTC QLQ-C30 [22] which is a standardised measure of QOL in cancer patients in general (including questions about physical and mental functioning and well-being), and the 25-item EORTC QLQ-PR25 [23] which is a prostate cancer-specific measure (which includes questions about urinary symptoms, sexual function, hormonal treatment-related symptoms etc.).

Mood is measured using the 14-item Hospital Anxiety and Depression Scale (HADS, [24]) which has two subscales for depressed mood and anxiety and was developed for use with medical samples. We expect that the intervention will have an effect on mood because hot flushes negatively affect patients’ mood and well-being.

Frequency of HF/NS, QOL and mood will all be measured at post-treatment and at the 6-month follow up assessment. Health economics questions, adapted from Beecham & Knapp [25]), including items on the number of consultations at primary and secondary care, absence from work, medical and non-medical treatments used across the duration of the trial, will be completed at the 6-month follow-up session.

#### Moderators

The 11-item Constructed Meaning Scale (CMS; [26]) measures whether, and/or how much, having a cancer diagnosis affects the way people feel about themselves, their relationships, and the future. We will examine whether men’s views about prostate cancer affect their response to the self-help treatment for HF/NS. This scale has previously been used in studies of people with cancer who vary in their tendency to perceive their cancer as a major threat [27], so there is a theoretical reason to predict that it might moderate the effectiveness of the intervention

The 4-item Emotional Control subscale of the Barriers to Help Seeking Scale (EC of the BHSS; [28]) measures a person’s willingness to express feelings and negative emotions. Including this measure enables us to explore whether beliefs about emotions are associated with outcome of the self-help treatment. Patients who are less willing to express emotions might be less amenable to the intervention which encourages an awareness of the relationships between cognitions, emotions and behaviours.

The 10-item Somatosensory Amplification Scale (SSAS; [29]) measures how sensitive individuals are to changes in their bodies. Including this as a moderator variable allows us to test whether heightened sensitivity affects the efficacy of the treatment. HF/NS may be exacerbated by an increased awareness of and attention to the body, so individuals who score highly on this scale might find it more difficult to follow some of the techniques of the treatment which aim to reduce attentional focus to HF/NS.

Finally, we employ the 10-item Revised Life Orientation Test (LOT-R; [30]) to examine whether trait optimism moderates the treatment outcome. This scale is used to assess how positive individuals’ outlook on life is, with a low score indicative of pessimism with regards to life events. Hence, individuals with low scores are not expected to benefit as much from the intervention as individuals with high scores on this scale.

#### Mediators

The Hot Flush Beliefs Scale [14] and The Hot Flush Behavior Scale [31] are used both before and after the treatment to check for any mediation effects. The scales, which were originally used for women with menopausal symptoms, have been modified for men (reduced to a combined total of 22 items). They measure types of beliefs and behaviours of individuals with HF/NS, some of which appear to be helpful and other less helpful [31]. Inclusion of these variables will help to clarify how the CBT intervention is working, i.e. whether specific beliefs and behaviours show change at post treatment and mediate improvement at follow-up.

The frequency of HF/NS is also measured by 24-48-hour ambulatory SSC monitoring (Bahr SSC monitor [Simplex Scientific; Middleton, WI, USA]) before and after treatment. The impact of the treatment upon subjective (frequency and problem-rating) and physiological measure of frequency will be an important secondary analysis and will help us to understand whether treatments are affecting the HF/NS threshold and/or symptom perception. We also record the self-reported frequency of relaxation practice, as well as treatment efficacy beliefs.

#### Statistical analysis

Primary efficacy analysis will be performed on the intent to treat population. The problem-rating of HF/NS at post treatment will be analysed using ANCOVA (i.e., analysis of covariance), adjusting for baseline problem-rating.

Secondary efficacy analyses: Secondary outcomes will be compared between groups as above. Possible mediators to response will also be investigated. The person performing the analyses will remain blind to the treatment grouping.

Safety analysis: The prevalence of specific adverse events is recorded and groups will be compared post-treatment.

Economic analysis: A descriptive analysis of economic data will be performed.

Statistical support may be sought from the Biostatistics Department, Institute of Psychiatry, King’s College London. Statisticians will not be informed of group allocation.

Power calculation: The sample size is calculated on the HF/NS Problem Rating Scale, estimating a mean of 5 (SD = 2.4) and a clinically relevant difference of 2 points [9]. A total sample size of 50, 25 in each group (allowing for 20% attrition) will have 90% power to detect a difference in mean HF/NS Problem-rating of 2 (a clinically significant change); based on results with women (no data on men exists) mean change of 2.87 and 0.77 in treatment and control groups respectively. However, we will recruit 70 (35 in each group) in order to power for secondary analyses, e.g. HF/NS frequency. We are recruiting from sites in the South East London Cancer Network and have badged the project with the NCRN. We estimate that 200 men receive ADT per year, that 35% (70) will meet inclusion criteria and that 16 months of recruitment should provide the numbers needed.

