Randomisation is carried out using the software Rand.exe version 6, which randomises participants to one of the two groups. Blocked stratification is used to ensure that the two groups do not differ on the potentially moderating variable of cancer type; depending on whether patients have localized or metastatic cancer (i.e., one that has spread to other organs), the intervention might be more or less effective. Patients with metastatic cancer may have lower levels of functioning and be less amenable to the intervention. Hence, stratifying for cancer type balances out any effects that might be due to this variable. Treatments undertaken during the follow-up period will be monitored in both arms of the trial.

Blinding: During the screening and baseline assessments the clinical psychologist is blind to group allocation. After this, the researcher generates a randomised allocation using Rand.exe and sends this to the clinical psychologist who in the next meeting informs the patient of allocation and then either starts the intervention or informs patients that they will continue with their usual care. The post-intervention assessments are then carried out by the researcher who is blind to group allocation. Figure 1 shows the trial procedure.

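### Randomisation is stratified by cancer type but the stated primary ANCOVA leaves that factor out; if cancer type is prognostic beyond baseline, the analysis is slightly conservative and loses some precision

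*Protocol article*

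**What the plan says.** The Procedure section of the protocol article states that "Blocked stratification is used to ensure that the two groups do not differ on the potentially moderating variable of cancer type". The reason given is that "Patients with metastatic cancer may have lower levels of functioning and be less amenable to the intervention", and the section concludes that "stratifying for cancer type balances out any effects that might be due to this variable".

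The Statistical analysis section says that the post-treatment problem-rating "will be analysed using ANCOVA (i.e., analysis of covariance), adjusting for baseline problem-rating". No other covariate is named. Secondary outcomes are to be compared between groups in the same way. Cancer type does not appear in the analysis section, nor among the scales listed under Moderators.

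The power statement works from "estimating a mean of 5 (SD = 2.4) and a clinically relevant difference of 2 points" and says that "A total sample size of 50, 25 in each group (allowing for 20% attrition) will have 90% power". It also cites a "mean change of 2.87 and 0.77 in treatment and control groups respectively" from work with women, a difference of 2.10. The recruitment target is then raised: "we will recruit 70 (35 in each group) in order to power for secondary analyses".

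**The concern.** Stratified blocking makes the arms nearly equal in their mix of localised and metastatic disease, so differences between the strata contribute little to the true sampling variation of the arm contrast. A model without the stratum still counts that between-stratum variation as residual error. If the strata differ in outcome after baseline adjustment, the model-based standard error therefore exceeds the true one. The confidence interval is then wider than it need be, the test runs below its nominal level, and the precision that the design bought is not fully used.

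The Procedure section appears to treat stratification as sufficient by itself. It secures balance between the arms, but it does not take the between-stratum variance out of the error term.

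The same model serves the secondary outcomes. These include quality-of-life measures of physical and mental functioning, where the lower functioning that the protocol anticipates in metastatic men could most plausibly appear.

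**Working it through.** **Inputs from the protocol article.** SD 2.4; target difference 2 points; 25 per group (50 in total) as calculated; 35 per group (70 in total) as planned; attrition 20%; 1:1 allocation, blocked within two strata.

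**Inputs assumed, because the article does not give them.** Correlation between baseline and post-treatment rating r = 0.5; metastatic share p = 30% or 50%; stratum difference after baseline adjustment g = 0, 1, 1.5 or 2 points; block size 4; two-sided 5% test.

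**Step 1: the plan's own power figure.** Power = Φ(δ / (σ√(2/n)) − z).
- Two-sided, σ = 2.4, n = 25: 2 / (2.4 × 0.2828) = 2.946; 2.946 − 1.960 = 0.986; power 0.838.
- Two-sided, n = 20 (25 less 20%): power 0.750. For 90%, 31 per group are needed.
- One-sided 5%, n = 25: 2.946 − 1.645 = 1.301; power 0.903.
- Two-sided ANCOVA, σ√(1 − r²): 0.895 at n = 25 with r = 0.4; 0.909 at n = 20 with r = 0.6.

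The stated 90% is thus reached only under assumptions that the article does not spell out. The present point does not depend on it.

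**Step 2: expected standard errors at 70 recruited.** About 28 per arm are analysed (35 × 0.8). Total SD is held at 2.4.
- Residual variance given baseline: 2.4² × (1 − 0.5²) = 5.76 × 0.75 = 4.32.
- Without the stratum term: SE ≈ √(4.32 × 2/28) = 0.56, whatever g is.
- With the term, the part g²p(1 − p) leaves the residual. For g = 2, p = 0.5: 4.32 − 1.00 = 3.32, SE ≈ √(3.32 × 2/28) = 0.49. For g = 2, p = 0.3: 4.32 − 0.84 = 3.48, SE ≈ 0.50. For g = 1, p = 0.5: 4.32 − 0.25 = 4.07, SE ≈ 0.54.

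**Step 3: simulation.** 4,000 trials per setting, stratified blocks, 20% random attrition, ANCOVA fitted without and with the term to the same data. Ranges cover p = 30% and 50%.

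| Recruited | Stratum difference | Power for 2 points, without | with | Type I error, without |
|---|---|---|---|---|
| 70 | 0 | 0.937 | 0.938 | 0.050 |
| 70 | 1 | 0.934-0.938 | 0.941-0.945 | 0.042-0.053 |
| 70 | 1.5 | 0.936-0.947 | 0.954-0.962 | 0.037-0.042 |
| 70 | 2 | 0.950-0.952 | 0.974-0.977 | 0.032-0.034 |
| 50 | 0 | 0.828-0.829 | 0.822-0.823 | 0.048-0.050 |
| 50 | 1 | 0.834-0.836 | 0.846-0.848 | 0.042-0.051 |
| 50 | 1.5 | 0.839-0.849 | 0.877 | 0.037-0.042 |
| 50 | 2 | 0.844-0.856 | 0.892-0.917 | 0.024-0.031 |

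At 70 recruited and g = 2, the average reported SE without the term is 0.56, while the estimate's actual standard deviation is 0.51. That gap is what makes the test conservative. With the term, both are 0.49-0.50. The simulation error on a type I rate near 5% is about √(0.05 × 0.95/4000) = 0.3 percentage points, so the small departures at g = 1 should not be read as real.

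**The case against.** **The protocol speaks mainly of moderation.** It calls cancer type a potential moderator and expects metastatic men to benefit less. That is a smaller treatment effect in one stratum, not a shift in outcome level. If only the effect differs between strata, by 1 or 2 points, with 70 recruited, 40% metastatic and r = 0.5, power without and with the term is 93.6% and 93.5%, or 91.0% and 91.7%. Type I error without the term is 4.6-4.7%. The loss then nearly vanishes. This stands, and it makes the point conditional. The remark on lower functioning is the only prognostic hint, and it does not concern hot-flush ratings given baseline.

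**A reader might infer a real shortfall in power.** Adding the stratum variance on top of SD 2.4 (40% metastatic, 2-point difference: 0.24 × 4 = 0.96) gives a residual variance of 4.32 + 0.96 = 5.28 and an SE of about √(5.28 × 2/28) = 0.61. Power for 2 points then appears to drop to about 91%. The article does not support this. It gives 2.4 as the SD of the scale, with no within-stratum qualifier, and adding 0.96 implies a total SD of √6.72 = 2.59. With total SD held at 2.4, power without the term does not fall materially below its value when strata do not differ. What is lost is a possible gain.

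**A 2-point stratum difference is large.** It equals the whole clinically relevant treatment effect, and nothing in the article shows it to be likely. This stands; it is the upper end of the range.

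**The article is condensed.** A fuller plan might list stratification factors, and the article does not say that baseline is the only covariate. But it does name the model and its covariate, and it describes stratification as what deals with cancer type. This limits the weight of the point without removing it.

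**Conclusion.** The point holds in a conditional and minor form. The design uses cancer type and the stated analysis does not. If cancer type predicts outcome beyond baseline, the reported standard error is too wide and the test conservative; if it does not, nothing is lost. It would be wrong to conclude that the primary result would be biased, that false positives would rise, or that the trial is underpowered because of this. At 70 recruited, power for a 2-point effect is about 93-95% without the term in every prognostic scenario examined.

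The gain in power from the term at 70 recruited is about 0, 1 and 2.5 percentage points for stratum differences of 0, 1 and 2 points; at 50 recruited it is at most about 6. These figures rest on r = 0.5, a metastatic share of 30-50% and 20% attrition at random. The correlation, the share and the stratum differences are assumptions, since the article gives none of them.

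**What to change.** State the primary model as ANCOVA of post-treatment problem-rating on arm, baseline problem-rating and cancer type (localised or metastatic, as recorded for randomisation). Use the same stratum term in the secondary-outcome models. Specify this before unblinding, so that the choice cannot look driven by the results.

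The variable is already held, so the cost is one degree of freedom. If cancer type turns out to be unrelated to outcome, no measurable power is lost at 70 recruited, and about 0.5 to 0.7 percentage points at 50. This change concerns the main-effect model only; it does not add a test of whether cancer type modifies the treatment effect.

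### Randomisation is stratified by cancer type, but the stated ANCOVA adjusts only for baseline problem-rating; adding the stratum aligns analysis with design at almost no cost

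*Protocol article*

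**What the plan says.** Under Procedure, the paragraph on randomisation states: "Blocked stratification is used to ensure that the two groups do not differ on the potentially moderating variable of cancer type". The reason given is clinical: "Patients with metastatic cancer may have lower levels of functioning and be less amenable to the intervention". The stated benefit is that "stratifying for cancer type balances out any effects that might be due to this variable".

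Under Statistical analysis, post-treatment problem-rating in the intention-to-treat population is to be "analysed using ANCOVA (i.e., analysis of covariance), adjusting for baseline problem-rating". The other outcomes take the same approach: "Secondary outcomes will be compared between groups as above". Cancer type is not mentioned in that section, and nowhere does the article say that it enters a model. The article gives neither the expected share of men with metastatic disease nor any figure linking cancer type to problem-rating.

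**The concern.** Stratified blocking makes the arms nearly alike on cancer type, so differences between the strata add almost nothing to the sampling variability of the treatment estimate. A model without the stratum does not know this. It treats the between-stratum variance as residual noise and reports a standard error larger than the estimator's true variability. The confidence interval is then too wide and the test rejects too seldom under the null.

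At stake is an efficient and correctly calibrated primary result. The same applies to every secondary comparison that inherits the model.

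**Working it through.** **The plan's own figure.** The sample size rests on "estimating a mean of 5 (SD = 2.4) and a clinically relevant difference of 2 points", and 25 per group "will have 90% power to detect a difference in mean HF/NS Problem-rating of 2". Alpha, sidedness and the baseline correlation are not stated. In the normal approximation, power = Φ(2 / (SD·√(2/n)) − z).

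- One-sided 5%, no baseline adjustment, n = 25: 2/(2.4·√(2/25)) = 2.946; Φ(2.946 − 1.645) = 90.3%.
- Two-sided 5%, ANCOVA with r = 0.6, n = 20 (25 less 20%): SD = 2.4·√(1 − 0.36) = 1.92; Φ(3.294 − 1.96) = 90.9%.
- Two-sided 5%, no baseline adjustment: 83.8% at n = 25.

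So the 90% can be reproduced under some readings. None of them involves cancer type.

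**Inputs for the check.** From the article: SD 2.4, difference 2, and 70 recruited with 20% attrition, giving 35 × 0.8 = 28 per arm, or 56 analysed. Assumed: baseline correlation r = 0.5; metastatic share p = 20-50%; strata differing by d = 0, 0.5, 1 or 2 points given baseline; two-sided 5%.

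**Closed form.** The residual variance after baseline is 2.4² × (1 − 0.5²) = 4.32. The stratum contributes p(1 − p)d².

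- If 2.4 is the overall SD, the stratum variance is part of the 4.32, and the ratio of reported SE without and with the stratum is √(4.32 / (4.32 − p(1 − p)d²)).
- If 2.4 is the SD within strata, it is added, and the ratio is √((4.32 + p(1 − p)d²) / 4.32).

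| d | p | p(1 − p)d² | Ratio, overall SD | Ratio, within-stratum SD |
|---|---|---|---|---|
| 0 | any | 0 | 1.00 | 1.00 |
| 0.5 | 20% / 50% | 0.04 / 0.0625 | 1.005 / 1.007 | 1.005 / 1.007 |
| 1 | 20% / 50% | 0.16 / 0.25 | 1.019 / 1.030 | 1.018 / 1.029 |
| 2 | 20% / 50% | 0.64 / 1.00 | 1.084 / 1.141 | 1.071 / 1.110 |

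The article does not say which SD it means. The excess is 2-3% at 1 point under either reading. At 2 points it is 8-14% under the first and 7-11% under the second.

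**Simulation.** This used 6,000 trials per setting, stratified blocks of 4 (assumed), 56 analysed and 2.4 as the overall SD. The Monte Carlo error on a 5% rate is √(0.05 × 0.95 / 6,000) = 0.3 points.

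| d | SE ratio (p = 20-50%) | Type I error without stratum | Power without stratum | Power with stratum |
|---|---|---|---|---|
| 0 | 1.00 | 4.6-5.3% | 93.9-94.4% | 93.8-94.3% |
| 1 | 1.02-1.03 | 4.6-4.8% | 94.2-94.3% | 94.5-95.0% |
| 2 | 1.08-1.14 | 2.6-3.3% | 95.1-95.7% | 96.6-97.8% |

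With 2.4 as the within-stratum SD and p = 40% (4,000 trials), power without and with the stratum is 92.9% and 93.5% at 1 point, and 91.0% and 94.2% at 2 points.

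**What is and is not lost.** At p = 30%, d = 2 and no treatment effect, the true sampling SD of the estimate is 0.505 without the stratum and 0.502 with it. The reported SE is 0.559 without and 0.501 with. The estimator keeps the benefit of balance; only its reported precision is wrong.

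**Sensitivity to r.** The article's only related figure is a test-retest r of 0.8 from studies with women. At r = 0.8 the residual variance is 5.76 × 0.36 = 2.07, and the excess at 1 point becomes 4-7%. Power at 28 per arm is then 99.9% before any stratum term, so little turns on it.

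**The case against.** The strongest objection is that this is a journal article. It does not say that baseline is the only covariate, and a fuller plan may list the stratification factor. That is possible. But the article is not silent: it states an adjustment, extends it to the secondary outcomes, and describes the stratification elsewhere without connecting the two. As published, model and design do not match.

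A second objection is that the harm is small and rests on assumed inputs. This stands. If cancer type is not prognostic given baseline, nothing is lost. A 2-point gap between strata would be as large as the trial's own clinically relevant difference.

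A reader might infer more than the documents support:

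- *That the primary p-value and interval are invalid.* They are not. The estimate is unbiased and the error is on the conservative side.
- *That stratifying was wasted.* It was not. Balance helps the estimator whatever model is fitted, and the article's stated aim was balance, not precision.
- *That the trial falls short of its power.* In the scenarios above, power without the stratum is at least 91.0%, above the 90% target. What is missed is a gain.
- *That the plan is faulty for not testing cancer type as a moderator.* Balancing a factor does not remove effect modification, so the wording on balancing out effects is loose, but rewording it changes no result. The Moderators section describes questionnaire scales, and cancer type's absence there does not prove that it will go unexamined. With about 11 metastatic and 17 localised men per arm (40% assumed), the interaction would have an SE of about √(4.32 × (2/11 + 2/17)) = 1.1 points, so it would show little.

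**Conclusion.** The point holds as a modest mismatch between design and analysis. The randomisation conditions on cancer type and the stated ANCOVA does not. The consequence is a conservative test and a wide interval, and only to the extent that cancer type predicts post-treatment problem-rating given baseline.

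For r = 0.5, 56 analysed and 20-50% metastatic, the excess in the reported standard error is nil to about 3% for stratum differences up to 1 point and about 8-14% at 2 points, with 0-3 percentage points of power forgone. The metastatic share, the stratum difference and the baseline correlation are all assumptions. The mismatch itself needs none of them.

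**What to change.** Under Statistical analysis, state the primary model as ANCOVA of post-treatment problem-rating on treatment, baseline problem-rating and cancer type (localised or metastatic, as used at randomisation). Apply the same structure to the secondary outcomes, each with its own baseline where one exists. If cancer type is left out on purpose, give the reason.

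The cost is one degree of freedom and a line of text, since the variable is already recorded for randomisation. If cancer type proves not to be prognostic, the simulations show practically no loss (power 93.8-94.3% with the stratum against 93.9-94.4% without). An exploratory treatment-by-cancer-type estimate with its confidence interval is optional and should be labelled as imprecise.
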